## Abstract

**Background:**

The identification of four Consensus Molecular Subtypes (CMS1–4) of colorectal cancer forms a new paradigm for the design and evaluation of subtype-directed therapeutic strategies. The most aggressive subtype - CMS4 - has the highest chance of disease recurrence. Novel adjuvant therapies for patients with CMS4 tumours are therefore urgently needed. CMS4 tumours are characterized by expression of mesenchymal and stem-like genes. Previous pre-clinical work has shown that targeting Platelet-Derived Growth Factor Receptors (PDGFRs) and the related KIT receptor with imatinib is potentially effective against mesenchymal-type colon cancer. In the present study we aim to provide proof for the concept that imatinib can reduce the aggressive phenotype of primary CMS4 colon cancer.

**Methods:**

Tumour biopsies from patients with newly diagnosed stage I-III colon cancer will be analysed with a novel RT-qPCR test to pre-select patients with CMS4 tumours. Selected patients (*n* = 27) will receive treatment with imatinib (400 mg per day) starting two weeks prior to planned tumour resection. To assess treatment-induced changes in the aggressive CMS4 phenotype, RNA sequencing will be performed on pre- and post-treatment tissue samples.

**Discussion:**

The development of effective adjuvant therapy for primary colon cancer is hindered by multiple factors. First, new drugs that may have value in the prevention of (early) distant recurrence are almost always first tested in patients with heavily pre-treated metastatic disease. Second, measuring on-target drug effects and biological consequences in tumour tissue is not commonly a part of the study design. Third, due to the lack of patient selection tools, clinical trials in the adjuvant setting require large patient populations. Finally, the evaluation of recurrence-prevention requires a long-term follow-up. In the ImPACCT trial these issues are addressed by including newly diagnosed pre-selected patients with CMS4 tumours prior to primary tumour resection, rather than non-selected patients with late-stage disease. By making use of the pre-operative window period, the biological effect of imatinib treatment on CMS4 tumours can be rapidly assessed. Delivering proof-of-concept for drug action in early stage disease should form the basis for the design of future trials with subtype-targeted therapies in colon cancer patients.

**Trial registration:**

ClinicalTrials.gov: NCT02685046. Registration date: February 9, 2016.

## Background

Mortality from colon cancer is almost invariably due to the development of distant metastases. In current practice, pathological (TNM stage) and clinical characteristics (age, co-morbidity) mainly determine the choice of adjuvant chemotherapy. However, these features have limited value in predicting which patients are at risk of developing metastases. In clinical trials, the five-year recurrence rate in stage III colon cancer patients is approximately 50% without adjuvant chemotherapy. With adjuvant treatment this is reduced to ~35%, implying that such treatment is only effective in a subgroup of patients [1]. Consequently, the majority of patients are currently being under- or over-treated. It is therefore important to be able to identify patients who are at high risk of recurrence and to develop more effective therapies to prevent relapse. Relapse-prevention trials in the adjuvant setting are challenging however, due to the long follow-up periods and the large numbers of patients that are required for sufficient statistical power. Prior evidence of drug activity and the availability of a companion diagnostic tool for patient selection could greatly facilitate the design and increase the quality of such studies.

Novel adjuvant therapies should be based on an understanding of the pathways that drive metastasis formation. Recent studies on molecular classification of colon cancer have provided insight into these pathways. Several research groups have independently developed classification systems for primary colon cancer based on gene expression profiles [2–8]. Cross-cohort analysis of the results has led to the identification of four consensus molecular subtypes (CMS1–4). Of these, CMS4 (~25% of colon cancers) is associated with a significantly worse disease-free and overall survival [9]. Novel treatment strategies for this subtype are thus particularly needed.

The pro-metastatic pathways that are upregulated in CMS4 provide opportunities for subtype-targeted therapy. CMS4 tumours are characterised by high expression of stem cell and mesenchymal genes, and a high stromal content [9]. We have previously shown that Platelet-Derived Growth Factor Receptors (PDGFRs) and KIT are highly expressed in mesenchymal-type colon tumours and that their expression strongly correlates with disease-free survival. Moreover, in vitro and in vivo inhibition of PDGFR and KIT tyrosine kinase signalling reduced invasiveness, metastatic potential and stem-like characteristics of mesenchymal-type colon cancer [10–12]. Based on these findings we hypothesise that patients with poor-prognosis mesenchymal-type colon cancers could benefit from treatment with imatinib, a tyrosine kinase inhibitor with high selectivity for PDGFR and KIT.

To test this hypothesis in a proof-of-concept study, we designed the ImPACCT trial (*Im*atinib as *P*re-operative *A*nti-*C*olon *C*ancer *T*argeted therapy). In ImPACCT, patients with CMS4 colon cancer are identified with a recently developed 4-gene RT-qPCR test that measures *PDGFRA, PDGFRB, PDGFC* and *KIT* expression levels in diagnostic tumour biopsies [13]. Pre-selected patients with CMS4 tumours are then treated with imatinib during the pre-operative window period (the time between initial cancer diagnosis and surgery). This allows comparison of pre-treatment diagnostic tumour biopsies with biopsies obtained from the resection specimen after treatment. The primary objective is to assess whether imatinib treatment reduces the aggressive phenotype of CMS4 tumours in colon cancer patients. ImPACCT may not only form the basis for future adjuvant studies with imatinib, but could also serve as a blueprint for other proof-of-concept studies with subtype-targeted therapies.

## Methods

### Study design

The ImPACCT trial is an open-label, multi-centre proof-of-concept study. The primary endpoint of this trial is the effect of imatinib treatment on tumour biology, which is a pharmacodynamic endpoint, and as such this trial could be deemed a phase II/translational trial. A study flow chart is depicted in Fig. 1.

**Fig. 1 Fig1:**
[figure not shown]
Study flow chart

### Objectives

The primary objective of this trial is to investigate the effects of treatment on pro-metastatic pathways in aggressive primary CMS4 tumours. RNA sequencing will be performed on pre- and post-treatment tissue samples to document imatinib-induced genome-wide gene expression changes.

Secondary objectives include: to assess the extent of inhibition of PDGFR- and KIT after imatinib treatment; to relate intra-tumoural imatinib pharmacokinetics (PK) to systemic imatinib concentrations; to relate the level of inhibition of PDGFR/KIT signalling and the extent of changes in gene expression to the systemic and intra-tumoural PK of imatinib and its active metabolite CGP74588; to assess changes in tumour markers during treatment by measuring the concentrations of plasma-CEA and circulating tumour DNA (ctDNA) and to study the effects of imatinib on organoid-forming potential. Finally, the effect of short-term exposure to imatinib immediately followed by bowel surgery on the complication rate will be monitored.

### Study population

All patients who are scheduled for a diagnostic colonoscopy on account of clinical suspicion of colon carcinoma will be approached for permission to obtain extra biopsies for this study in case a tumour is found in the colon. These biopsies are pre-screened with the new RT-qPCR test that predicts the chance of a tumour being CMS4, based on the combined expression of imatinib targets *PDGFRA, PDGFRB, PDGFC* and *KIT* [13]. If the predicted chance of CMS4 in the biopsies is 50% or higher, patients will be approached for imatinib therapy. The study population that undergoes treatment with imatinib will thus consist of treatment-naïve newly diagnosed colon cancer patients with a tumour with a high probability of having the CMS4 phenotype. In- and exclusion criteria for enrolment in the second part of the trial (imatinib therapy) are listed in Table 1.

**Table 1 Tab1:** In- and exclusion criteria for treatment with imatinib

Inclusion criteria	Exclusion criteria
- Male or female aged ≥18 years; - Histologically proven adenocarcinoma of the colon; - Completed cancer staging with CT-abdomen and CT-thorax/X-thorax according to hospital’s standard of care; - Confirmed eligibility for surgery with curative intent as deemed by the hospital’s multidisciplinary board review; - Test positive for CMS4 subtype; - ≥4 properly stored pre-treatment biopsies for gene expression analysis/ELISA; - WHO performance status 0 or 1; - Adequate haematology status and organ function (defined as: normal creatinine clearance (≥60 ml/min (MDRD)), ALAT within 2.5× upper limit of normal (ULN), PT-INR < 1.5, leukocytes >1,5*10^9/L, Hb > 6.0 mmol/L, platelets >100*10^9/L); - Willingness and ability to comply with scheduled visits, treatment plans and laboratory tests; - Provision of written informed consent.	- The presence of synchronous distant metastases; - Current hospital standard of care dictates that subject should undergo any neoadjuvant therapy; - Concurrent participation in another clinical trial using any medicinal product, or participation in such a trial in the period of three months prior to the current trial; - Women who are pregnant, plan to become pregnant or are lactating during the study or for up to 30 days after the last dose of imatinib; - Known HIV or Hepatitis B/C infection; - Known symptomatic congestive heart failure; - Co-morbidity requiring concomitant treatment with drugs that act as strong inducers of CYP3A4 or with drugs with a narrow therapeutic range influenced by imatinib.

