### Study procedures

Patients pre-selected with the RT-qPCR test will be screened by a medical oncologist for inclusion in the second part of this study. Included patients will receive treatment with imatinib starting two weeks prior to planned tumour resection. Imatinib will be administered orally at a daily dosage of 400 mg for two weeks, with the last dose given within 12 h before surgery. Patients are requested to register drug intake and any adverse events in a patient diary. Before the start of imatinib therapy and at the end of the treatment period, blood samples will be obtained to measure ctDNA and plasma-CEA. Plasma imatinib trough levels will be determined on the day of surgery. Immediately following tumour resection, biopsies will be taken from the surgical specimen (post-treatment biopsies). Gene and protein expression of the pre-treatment biopsies (from colonoscopy) and post-treatments biopsies will be compared to assess the effects of imatinib therapy on PDGFR- and KIT-signalling and on the mesenchymal gene expression profile. After surgery, patients will be monitored according to standard of care. Any postoperative adverse events up until 14 days after discontinuation of study medication (end of study) will be documented.

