### Sample size calculation

This study is designed as a proof-of-concept study with multiple outcomes of interest. We expect the effect size of imatinib treatment on the various parameters to be very high, since we specifically select patients who express high levels of the drug targets. However, we are aware of possible factors that may reduce the observed effect size. This includes intra-tumour heterogeneity in target expression – causing potential misclassification – and variation in drug distribution throughout the tumour and between patients. Therefore, we anticipate a medium to high Cohen effect size for the primary endpoint (i.e. Cohen’s effect size of 0.65). To demonstrate such an effect, we need to include 27 (evaluable) patients, based on a two-sided paired-samples t-test with a significance level α of 0.05 and power 1-β of 90%. We specifically chose this high power in order not to dismiss effects that are potentially relevant for further development of imatinib therapy in colorectal cancer patients. Given that approximately 25% of colon cancers are CMS4, at least 4*27 = 108 eligible patients with newly diagnosed colon cancer will need to be pre-screened with the RT-qPCR test. Since <10% of the patients undergoing colonoscopy are diagnosed with colon cancer, at least 1.100 patients will have to be approached for pre-screening informed consent.

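### Selection on high target-gene readings and the paired baseline both draw on the colonoscopy biopsies, with none reserved, so regression to the mean can mimic a fall in the CMS4 signature

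*Protocol article*

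**What the plan says.** Selection. Under Study population, extra biopsies are taken at diagnostic colonoscopy and tested: "These biopsies are pre-screened with the new RT-qPCR test that predicts the chance of a tumour being CMS4". The test combines PDGFRA, PDGFRB, PDGFC and KIT, which the Background describes as measured through "expression levels in diagnostic tumour biopsies". The entry rule is "If the predicted chance of CMS4 in the biopsies is 50% or higher, patients will be approached for imatinib therapy".

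Baseline. Under Study procedures: "Gene and protein expression of the pre-treatment biopsies (from colonoscopy) and post-treatments biopsies will be compared to assess the effects of imatinib therapy". The Background describes the same comparison: "This allows comparison of pre-treatment diagnostic tumour biopsies with biopsies obtained from the resection specimen after treatment".

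Stored tissue. Table 1 requires "≥4 properly stored pre-treatment biopsies for gene expression analysis/ELISA". It does not say whether these include the biopsies that were tested for selection.

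Test. Statistical analyses specifies a paired t-test or Wilcoxon signed-rank test of whether CMS4-associated signature expression changed. No untreated group is described.

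Sampling variability. The Sample size calculation lists reasons why the observed effect might be smaller than hoped: "This includes intra-tumour heterogeneity in target expression", with possible misclassification as a result. It mentions no effect in the other direction.

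**The concern.** A tumour that enters because its biopsy read high will, on average, have been sampled somewhat above its own mean. A later sample from the same tumour, untreated, will then tend to read lower. The selection score and the endpoint are meant to capture the same phenotype, so they should be positively correlated, and the fall carries over to the signature. It points the way the trial hopes to see.

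With one arm and a test against zero change, this fall cannot be separated from a drug effect. Heterogeneity and misclassification, which the sample size section treats only as diluting the effect, can therefore also create one. More than a p-value is at stake: the Discussion says that the estimated effect size may drive the design of a larger randomised phase II trial.

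**Working it through.** **Step 1. The plan's own figure.** Inputs from the Sample size calculation: effect size 0.65, two-sided α 0.05, power 90%, paired t-test. Exact noncentral-t power is 88.96% at n = 26 and 90.15% at n = 27. The stated 27 is correct. The issue is what the test can attribute to the drug.

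**Step 2. Model with no drug effect.** From the protocol article: n = 27, two-sided 0.05, about 25% of colon cancers CMS4. Assumed, because the article gives no values:
- ICC, the correlation between two biopsies of one tumour: 0.6 to 0.9.
- r, the correlation of test score with RNA-seq signature in the same tissue: 0.6 to 0.8.
- Selection of the top 25% of scores. The actual rule is a predicted probability, not a percentile.

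Signature in a biopsy = T + e, with Var(T) = ICC and Var(e) = 1 − ICC. Score S = r × (signature in the selecting tissue) + noise, with variance 1. The mean score of the top 25% is i = φ(0.674)/0.25 = 1.271, and k = i(i − 0.674) = 0.758.

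For change d = post − pre, Var(d) = 2(1 − ICC) before selection. Let c be the size of the covariance of d with S. Then:
- expected fall = c × i
- SD of d after selection = √(Var(d) − c²k)
- spurious standardised change dz = c × i / SD

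**Step 3. Middle case, ICC 0.7 and r 0.8.**
- One biopsy in both roles: c = 0.8 × 0.3 = 0.24. Fall = 0.24 × 1.271 = 0.305. SD = √(0.6 − 0.24² × 0.758) = 0.746. dz = 0.41; the test rejects in 54% of trials.
- Four biopsies averaged at each time point, all four reused as baseline, r held at 0.8 for the averaged reading: error variance 0.3/4 = 0.075, total variance 0.775, c = 0.8 × 0.075/√0.775 = 0.0682. Fall = 0.087. SD = √(0.15 − 0.0682² × 0.758) = 0.383. dz = 0.23; rejection 21%.
- Separate single baseline biopsy, half the error variance shared within the colonoscopy: c = 0.8 × 0.15 = 0.12. Fall = 0.153. SD = √(0.6 − 0.12² × 0.758) = 0.768. dz = 0.20; rejection 17%.
- Separate baseline biopsy, independent error: c = 0, dz = 0; rejection 5%.

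**Step 4. Full range.** Each cell shows the percentage of no-effect trials with p < 0.05 and, in brackets, the spurious dz. Rejection rates come from simulation with at least two million tumours per cell; simulated dz agrees with the formula.

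| Baseline tissue | r | ICC 0.9 | ICC 0.8 | ICC 0.7 | ICC 0.6 |
|---|---|---|---|---|---|
| One biopsy, both roles | 0.8 | 21 (0.23) | 38 (0.33) | 54 (0.41) | 67 (0.48) |
| One biopsy, both roles | 0.6 | 14 (0.17) | 23 (0.25) | 32 (0.30) | 41 (0.35) |
| Four averaged, reused | 0.8 | 9 (0.12) | 14 (0.18) | 21 (0.23) | 28 (0.28) |
| Four averaged, reused | 0.6 | 7 (0.09) | 10 (0.13) | 14 (0.17) | 18 (0.21) |
| Separate, half the error shared | 0.8 | 9 (0.11) | 13 (0.16) | 17 (0.20) | 21 (0.23) |
| Separate, half the error shared | 0.6 | 7 (0.09) | 9 (0.12) | 12 (0.15) | 14 (0.17) |
| Separate, independent error | both | 5 (0) | 5 (0) | 5 (0) | 5 (0) |

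Except in the last row, nearly all the excess over 5% is in the direction of a lower signature.

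**The case against.** The article never says that one physical biopsy, or one RNA extract, serves both purposes. Table 1 lists a positive test and the stored biopsies as separate criteria, so a fair reading is that at least four biopsies are held for the endpoint assays apart from the tested tissue. The article is condensed, its flow chart was not visible in the copy reviewed, and allocation of tissue to assays may be set out in the full protocol. The text also speaks of biopsies in the plural, so the single-biopsy rows are a worst case. Finally, this is a proof-of-concept study that also measures receptor phosphorylation and drug concentrations, so it does not rely on the signature test alone.

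Most of this stands, and it limits the claim. A reader might infer that reuse of the same tissue is established, or that the trial's 5% error rate is known to fail. The documents support neither: reuse is the natural reading of the text but is not stated, and no repeatability figure is given. A reader might also infer that a separate baseline biopsy restores the 5% rate in all cases. It does so only if its sampling error is independent of the selecting biopsy.

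Two things remain. As described, the colonoscopy biopsies have both roles with no separation, and the sample size section treats heterogeneity only as dilution. Averaging four biopsies reduces the inflation but leaves it above 5% in every case examined. The secondary measurements do not protect the primary test.

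**Conclusion.** The concern holds conditionally. If the tissue that qualified the patient is also the baseline, the paired test is biased towards a reduction. Over the assumed ranges, the false-positive rate is about 14% to 67% with a single biopsy in both roles (dz 0.17 to 0.48, against a planned 0.65) and about 7% to 28% with four biopsies averaged (dz 0.09 to 0.28). With separate baseline biopsies and independent error it is about 5%. ICC, r, the 25% cut and the averaging scheme are all assumptions, so only the ranges are supportable. The sample size of 27 is not in question. Should-fix, with moderate confidence.

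**What to change.** - State that the RNA-seq and protein baseline comes only from stored pre-treatment biopsies whose RT-qPCR result did not enter the eligibility decision, taken where possible from a different part of the tumour.
- Exclude PDGFRA, PDGFRB, PDGFC and KIT from the primary signature, or report the result with and without them. This is not enough alone, because co-expressed genes regress too.
- Report patients who have only tested biopsies in a sensitivity analysis.
- Amend the sample size text to say that heterogeneity and misclassification can also produce an apparent fall.
- State as limitations that separate biopsies reduce but may not remove the bias (about 7% to 21% rejection if half the sampling error is shared within the colonoscopy), and that they do not address differences between colonoscopy and resection sampling. A pre/post change therefore cannot be attributed to imatinib on the paired test alone.

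Cost: a sample-handling rule and a few sentences. At least four stored biopsies are already required and n stays at 27. The downside is that fewer biopsies inform the CMS4 call. The rule has to be set before the tissue is used up.

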### Study procedures

Patients pre-selected with the RT-qPCR test will be screened by a medical oncologist for inclusion in the second part of this study. Included patients will receive treatment with imatinib starting two weeks prior to planned tumour resection. Imatinib will be administered orally at a daily dosage of 400 mg for two weeks, with the last dose given within 12 h before surgery. Patients are requested to register drug intake and any adverse events in a patient diary. Before the start of imatinib therapy and at the end of the treatment period, blood samples will be obtained to measure ctDNA and plasma-CEA. Plasma imatinib trough levels will be determined on the day of surgery. Immediately following tumour resection, biopsies will be taken from the surgical specimen (post-treatment biopsies). Gene and protein expression of the pre-treatment biopsies (from colonoscopy) and post-treatments biopsies will be compared to assess the effects of imatinib therapy on PDGFR- and KIT-signalling and on the mesenchymal gene expression profile. After surgery, patients will be monitored according to standard of care. Any postoperative adverse events up until 14 days after discontinuation of study medication (end of study) will be documented.

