Experimental therapy during the pre-operative window period could potentially lead to an increase in postoperative complications. However, based on two phase II trials that evaluated the use of neoadjuvant imatinib therapy for otherwise irresectable or metastatic GIST, we believe it is safe to administer the last dose of imatinib within 12 h before surgery. In these trials imatinib was administered for several months and stopped one day prior to surgery. Both studies concluded that this approach was feasible, and the reported postoperative complications were acceptable and not out of the ordinary considering the extensive abdominal surgery [25, 26].

Instead of assessing a clinical endpoint (e.g. disease-free survival), this proof-of-concept trial investigates a surrogate endpoint (gene expression changes) to demonstrate a ‘biological’ treatment effect. This endpoint requires a relatively limited sample size and can be determined after only two weeks of therapy, which limits the burden placed on participants. If treatment effects are indeed demonstrated, knowledge of the size of the effect on tumour biology can be used to drive the design of a larger randomised phase II trial.

The design of the ImPACCT trial presented here allows rapid evaluation of the mechanism of action of a targeted therapy in a subtype-stratified patient population by analysis of paired pre- and post-treatment biopsies, without interfering with or delaying standard-of-care, by making use of the pre-operative window period. This design can serve as a blueprint for subtype-directed proof-of-concept trials in colon cancer, with the ultimate goal of designing effective adjuvant therapy that eradicates occult metastases.

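### Recording of postoperative events stops about 14 days after surgery, so later complications are lost from the complication-rate objective

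*Protocol article*

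**What the plan says.** Three parts of the Protocol article bear on this point.

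- **Objectives.** The last item among the secondary objectives is that "the effect of short-term exposure to imatinib immediately followed by bowel surgery on the complication rate will be monitored". No time horizon is attached to that rate.
- **Study procedures.** Treatment is timed against the operation: "Included patients will receive treatment with imatinib starting two weeks prior to planned tumour resection", "with the last dose given within 12 h before surgery". Aftercare is routine: "After surgery, patients will be monitored according to standard of care". The recording rule is then: "Any postoperative adverse events up until 14 days after discontinuation of study medication (end of study) will be documented".
- **Discussion.** The risk is acknowledged: "Experimental therapy during the pre-operative window period could potentially lead to an increase in postoperative complications". The article goes on to argue that the approach is safe, citing two trials of imatinib before surgery for gastrointestinal stromal tumours.

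Statistical analyses gives no test, threshold or reference rate for complications.

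**The concern.** The objective is about complications of an operation, but the recording window is tied to the drug and closes two weeks after the last dose. Any event that first appears after that point is outside the trial's record, even if routine care detects it. The error has one direction: a shorter window can lose affected patients but cannot add any.

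At stake is how the safety result can be read. The study has one arm, so an effect on the complication rate can be judged only against an outside rate. That requires a defined horizon counted from surgery, and the article gives none. Without a label, a two-week rate could be taken as the overall postoperative rate. Events not recorded prospectively may also be hard to recover later.

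**Working it through.** **Inputs from the Protocol article**

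- Window: 14 days after discontinuation (Study procedures).
- Last dose: 0 to 12 h before surgery (Study procedures).
- Treatment: 14 days, ending at the planned resection (Study procedures).
- Patients: "we need to include 27 (evaluable) patients, based on a two-sided paired-samples t-test" (Sample size calculation).
- Plasma half-life of imatinib: 18 h (Discussion).

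**Step 1. The plan's own figure.** The power of the two-sided paired t-test comes from the noncentral t distribution with n − 1 degrees of freedom and noncentrality 0.65 × √n. It is 88.96% at n = 26 and 90.15% at n = 27, so the stated 27 is reproduced. It is a figure for the primary endpoint. Here it serves only as an approximate denominator for the complication rate.

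**Step 2. Length of postoperative observation.** For a patient on schedule:

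- last dose at surgery: 14 − 0 = 14.0 days;
- last dose 12 h before surgery: 14 − 0.5 = 13.5 days.

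If a patient stops imatinib early and the operation keeps its planned date, a stop on day k of 14 leaves about k + 14 − 14 = k days after surgery. That is about 10, 7 or 3 days for a stop on day 10, 7 or 3. The drug anchor therefore makes follow-up unequal between patients, which is a further reason to count from surgery.

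**Step 3. Possible size of the loss.** Let p be the true rate over a longer horizon and f the share of affected patients whose first event comes after the window closes. Neither is in the documents. The assumed ranges are p = 20–40% and f = 0–30%.

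- Patients missed = 27 × p × f
- Recorded rate = p × (1 − f)
- Standard error of the rate = √(p(1 − p)/27)

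| p | f | Missed of 27 | Recorded rate | Standard error at p |
|---|---|---|---|---|
| 20% | 0% | 0 | 20% | 7.7 points |
| 20% | 30% | 1.6 | 14% | 7.7 points |
| 30% | 10% | 0.8 | 27% | 8.8 points |
| 30% | 30% | 2.4 | 21% | 8.8 points |
| 40% | 30% | 3.2 | 28% | 9.4 points |

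The loss runs from zero to about 3 patients.

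**Step 4. Precision at n = 27.** Exact (Clopper-Pearson) 95% intervals are:

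- 0/27: upper limit 1 − 0.025^(1/27) = 12.8%;
- 8/27 (30%): 13.8% to 50.2%.

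The rate will be imprecise whichever window is used.

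**The case against.** The strongest reply is that a 14-day rate is a valid estimate of 14-day complications. The article fixes no longer horizon and plans no comparison with a longer-window rate, so nothing in it makes 14 days wrong. The window also has a plausible pharmacological basis: 14 × 24 / 18 = 18.7 half-lives, well beyond elimination of the parent drug. The objective is secondary and only monitored. The likely shift is also small beside the sampling error: 8/27 and 6/27 have exact 95% intervals of about 14–50% and 9–42%, which largely overlap.

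Much of this stands. It limits the point to a modest improvement and rules out saying that harm *is* understated. It does not remove the mismatch. Drug elimination is a reason to choose a window for drug reactions, whereas the objective concerns the sequel of an operation. Wide intervals reflect chance, while the loss of late events runs in one direction only.

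One could also say that the full protocol may provide longer follow-up. The article does not leave the matter open, however: it states a cut-off and calls it the end of the study.

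A reader might infer three stronger points, which the documents do not support:

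- **That the decision on a larger trial rests on this rate.** The Discussion ties the design of a later randomised trial to the size of the effect on tumour biology.
- **That the plan itself points to 30 days.** The phrase "for up to 30 days after the last dose of imatinib" in Table 1 belongs to the exclusion for pregnancy and lactation and says nothing about follow-up of adverse events.
- **That pre-screened patients operated on without imatinib could serve as a reference.** Many would be test-negative, ineligible or unwilling, so they are not comparable. The permission described in Study population is for extra biopsies, with no mention of surgical outcomes.

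**Conclusion.** The point holds as a limited one. For a patient on schedule, recording ends 13.5 to 14.0 days after surgery, and complications that first occur later are lost to an objective that concerns the complication rate. Relative to any longer horizon, the recorded rate can only be equal or lower.

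The size of the loss cannot be derived from the documents. The range of 0 to about 3 of 27 patients rests wholly on the assumed rate of 20–40% and late share of 0–30%, and zero is within it. The primary conclusion on gene expression is unaffected.

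**What to change.** 1. Count postoperative events from the date of surgery, for every treated patient, over a fixed and longer horizon. Thirty days is offered as an example of a data-collection window; it is not a figure from the plan.
2. Take complications, readmissions, reoperations and deaths from the standard-of-care follow-up already planned, and move the end of study for safety to match.
3. Report the rate with its window and an exact 95% confidence interval.
4. If the window is not extended, label the result as a rate to about 14 days after surgery.

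With a 30-day window the cost is about 30 − 14 = 16 more days of record review per patient and a slightly later end of study. No visit or procedure is added.
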